### Objectives and endpoints

The primary endpoint is the between-group difference in mPAP at rest, measured by RHC at 16 weeks. Secondary endpoints for the primary study objective are outlined in table 1.

**Table 1 T1:** Secondary outcomes for the primary study objective

Objectives	Secondary endpoints
To investigate if discontinuation of riociguat is non-inferior to its continuation in CTEPH patients with mPAP <30 mmHg post-BPA	Efficacy endpoints: Between-group differences at 16 weeks for the following parameters in hierarchical order: NT-proBNP (assessed for non-inferiority) 6MWD (assessed for non-inferiority) PVR Cardiac index Between-group differences at 16 weeks in exercise capacity in post hoc analysis: CPET variables: oxygen uptake, workload, heart rate, respiratory exchange ratio, ventilation, oxygen saturation, oxygen pulse, equivalent carbon dioxide Change in modified Borg dyspnoea scale Safety endpoints: Between-group differences at 16 weeks in the following parameters: Number of adverse events and severe adverse events Proportion of participants with mPAP ≥38 mmHg at RHC Proportion of participants meeting the clinical worsening criteria at week 8 Feasibility of the strategy: Is TTE sufficient to replace RHC at the end of study follow-up? The correlation between TTE and RHC parameters Right ventricular systolic pressure Tricuspid annular plane systolic excursion Proportion of participants missed by TTE with mPAP ≥38 mmHg at 16 weeks RHC Is the discontinuation strategy feasible for implementation in clinical practice? Proportion of participants missed by the clinical worsening criteria with mPAP ≥38 mmHg at 16 weeks Participants' satisfaction with the protocol

BPA, balloon angioplasty; CPET, cardiopulmonary exercise testing; CTEPH, chronic thrombo-embolic pulmonary hypertension; mPAP, mean pulmonary artery pressure; 6MWD, 6-min walking distance; NT-proBNP, N-terminal pro-B-type natriuretic peptide; PVR, pulmonary vascular resistance; RHC, right heart catheterisation; TTE, transthoracic echocardiography; WHO, world health organisation.

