### Statistical analysis

All analyses will be performed using R (R Foundation for Statistical Computing, Vienna, Austria). Continuous variables will be summarised as mean±SD or median (IQR) as appropriate; categorical variables as counts and percentages. Normality will be assessed using histograms and Q–Q plots. Skewed variables will be log-transformed when necessary.

The null hypothesis is that riociguat discontinuation is inferior to continuation. NI will be concluded if the upper bound of the two-sided 95% CI for the baseline-adjusted between-group difference does not exceed the predefined NI margin. A one-sided significance level of α=0.025 will be used.

A secondary analysis of the primary endpoint (mPAP at 16 weeks) will include an analysis of covariance (ANCOVA), with baseline mPAP as a covariate. Treatment group will be included as the main effect, with riociguat dose and incident/prevalent status included as fixed factors to account for stratification at randomisation. To control the type I error rate, hierarchical testing will be applied. Secondary continuous outcomes will be analysed using ANCOVA or linear regression adjusted for baseline values. Binary outcomes will be analysed using χ^2^ or Fisher’s exact tests. Ordinal outcomes will be analysed using stratified Wilcoxon tests or linear mixed models for repeated measures, as appropriate. All estimates will be reported with two-sided 95% CIs.

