### Analysis set

The primary analysis will be conducted in the per-protocol population, as an intention-to-treat (ITT) analysis can be considered anticonservative in a NI study testing discontinuation. Participants who restart riociguat due to clinical worsening will be analysed in the continuation group. As a secondary analysis, we will perform an ITT analysis according to randomised allocation, reflecting the clinical discontinuation strategy including re-initiation and testing the safety of the stopping strategy. In addition, two exploratory analyses will be performed: a modified ITT analysis excluding participants who restarted riociguat from the discontinuation group to explore outcomes among patients who tolerate treatment withdrawal without re-initiation, and a subgroup analysis comparing participants who restarted riociguat with the continuation group to assess haemodynamic response following re-initiation. Non-compliant patients who meet protocol violations will be excluded as part of the modified per-protocol (PP) analysis. Missing data will not be imputed. However, participants who withdraw before the week 8 clinical worsening assessment because of clinical deterioration, or for whom the reason for withdrawal is unknown, will be conservatively classified as having experienced clinical worsening.

To account for potential loss of participants from the primary per-protocol analysis due to clinical worsening, predefined scenarios were incorporated into the statistical analysis planning. Based on power simulations, the study is expected to retain approximately 80% power if up to 35% of participants are lost from the intervention group. To mitigate the risk of insufficient power, the randomisation ratio will be reassessed after inclusion of 50% of the planned sample size. If ≥30% or ≥40% of participants in the discontinuation group have restarted riociguat at that point, the randomisation ratio will be adaptively adjusted from 1:1 to 2:1 or 3:1, respectively, in favour of the discontinuation group. If ≥50% of participants in the discontinuation group experience clinical worsening, the study will be terminated for safety reasons, as such a rate is considered clinically unacceptable.

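### The only safeguard for early withdrawal protects a week-8 safety proportion, not the primary mPAP test, where unimputed losses from the discontinuation arm could favour non-inferiority

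*Protocol article*

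**What the plan says.** All of the relevant handling is fixed in the Analysis set section of the protocol article.

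- On missing values the statement is general: "Missing data will not be imputed".
- The one exception concerns "participants who withdraw before the week 8 clinical worsening assessment because of clinical deterioration, or for whom the reason for withdrawal is unknown", who "will be conservatively classified as having experienced clinical worsening". No arm is named, so it applies to both.
- On the analysis population: "The primary analysis will be conducted in the per-protocol population". An ITT analysis by randomised allocation is secondary.
- On restarts: "Participants who restart riociguat due to clinical worsening will be analysed in the continuation group".

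Under Objectives and endpoints, "The primary endpoint is the between-group difference in mPAP at rest, measured by RHC at 16 weeks". Clinical worsening appears in Table 1 as a safety endpoint: "Proportion of participants meeting the clinical worsening criteria at week 8". The Statistical analysis section gives the test for such outcomes: "Binary outcomes will be analysed using χ^2^ or Fisher’s exact tests". According to the Abstract, NI is tested only for mPAP, NT-proBNP and 6-minute walk distance.

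**The concern.** The exception recognises that withdrawal may reflect deterioration, but it acts only on a safety proportion. Reclassifying a withdrawn participant as worsened supplies no week-16 mPAP. That participant has not restarted riociguat either, so the rule on restarts does not apply. Without a week-16 catheterisation and without imputation, the participant is absent from the primary test. The ITT analysis does not bring them back, because the no-imputation statement covers it too. The Table 1 proportion with mPAP of 38 mmHg or more at catheterisation loses the same people.

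Selective loss is plausible in an open-label withdrawal trial. Clinical worsening requires three criteria at once, so a participant who declines on one or two does not meet the definition and may simply leave. The article itself plans for up to 35% of the intervention group being lost from the per-protocol analysis through clinical worsening. It treats this as a question of power, although loss related to deterioration also raises a question of bias. At stake is a conclusion of NI on mPAP reached because the participants with the largest rebound were not measured.

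**Working it through.** **Inputs from the article.** One-sided alpha 0.025, power 90%, SD 4.9 mmHg, margin 4 mmHg, 74 participants randomised 1:1, 10% dropout (Randomisation and allocation; Sample size calculation). SD of mPAP change 3.8 mmHg and correlation −0.08, which I read as the correlation between the first mPAP and its later change (Non-inferiority margin).

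**Assumed.** The article gives no dropout by arm or reason, no mPAP for those who leave and no worsening rates.

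**Step 1: the plan's own figure.** n per group = (1.960 + 1.282)² × 2 × 4.9² / 4² = 10.51 × 48.02 / 16 = 31.5, rounded up to 32. The stated 64 reproduces. With 37 per arm and 10% loss, 37 × 0.9 = 33.3; I use 33.

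**Step 2: bias.** If a fraction m of the discontinuation arm is missing and their mPAP would lie g above completers, the difference is understated by m × g. With m = 0.10: g = 4 gives 0.4 mmHg and g = 8 gives 0.8 mmHg.

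**Step 3: standard error.** The NI criterion uses a baseline-adjusted difference, but the trial is sized on an unadjusted SD, so both are shown.
- Unadjusted: 4.9 × √(2/33) = 1.206.
- Adjusted: residual SD = 3.8 × √(1 − 0.08²) = 3.788; 3.788 × √(2/33) = 0.933.

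**Step 4: chance of declaring NI at a true difference of 4 mmHg** = Φ(bias/SE − 1.96).

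| Assumed gap | Bias | Adjusted | Unadjusted |
|---|---|---|---|
| 0 (random loss) | 0 | 2.5% | 2.5% |
| 4 mmHg | 0.4 | 6.3% | 5.2% |
| 8 mmHg | 0.8 | 13.5% | 9.7% |

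**Step 5: simulation as a check.** 37 per arm, SD 4.9, true difference 4 mmHg, t-based 95% CI, 40,000 runs per scenario. Four controls are lost in every row, at random unless stated.

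| Loss | Bias in the difference (mmHg) | NI declared |
|---|---|---|
| 4 per arm at random | 0.00 | 2.5% |
| 4 stoppers, loss correlated 0.5 with mPAP | −0.50 | 6.6% |
| 2 highest-mPAP stoppers | −0.56 | 7.8% |
| 4 highest-mPAP stoppers | −0.99 | 14.9% |
| 4 highest in each arm | 0.00 | 4.3% |
| 4 stoppers at random, 4 highest controls | +0.99 | 0.4% |

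**Step 6: the worsening proportion.** If a further share d is reclassified, the observed proportion is p + (1 − p)d. Assume true rates of 20% (stop) and 5% (continue), a 15-point difference.
- 10% reclassified in each arm: 28.0 − 14.5 = 13.5 points.
- 10% stop, 5% continue: 28.0 − 9.75 = 18.25 points.
- 5% stop, 10% continue: 24.0 − 14.5 = 9.5 points.

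The rule can therefore move this difference in either direction.

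**The case against.** A reader might infer that both handlings favour NI: the worsening rule because it also counts unknown-reason withdrawals in the continuation arm, and the mPAP analysis because it drops missing values. The documents do not support that reading.

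- Clinical worsening has no margin and no NI test, so reclassification cannot itself yield an NI conclusion. Step 6 shows no fixed direction: if stoppers withdraw more often, the rule counts against discontinuation.
- For the termination rule at 50% worsening, which counts the discontinuation arm only, the classification is indeed conservative. At an assumed true rate of 40%, the chance of at least 9 of 18 rises from 0.26 to 0.46 when 10% are reclassified.
- Ending at week 8 matches the endpoint's own definition. It is a limit of coverage and not a contradiction.
- Scoring unknown-reason withdrawals as worsened in one arm only would be wrong as the main comparison. With equal true rates of 5% and 10% such withdrawals, it gives 0.05 + 0.95 × 0.10 = 14.5% against about 5%, an artificial gap.

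All of this stands. On mPAP, it can fairly be said that monthly contacts, unscheduled evaluations and restarts should keep many deteriorating participants in view, and that ITT includes restarters who are measured. This narrows the group to those with no week-16 catheterisation, but does not remove it. The 8 mmHg gap is also demanding, at about 8/4.9 = 1.6 SD, and needs all 10% dropout in that arm to be of this kind.

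A last objection is that missing-data sensitivity analyses belong in the analysis plan, which is not shown. Their absence is not the point here. The article states a rule against imputation, and that rule can be judged as written.

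**Conclusion.** The point holds in conditional form. As written, withdrawal with no week-16 catheterisation removes a participant from both mPAP analyses, and the only safeguard acts on a different endpoint. If such losses are concentrated among deteriorating participants in the discontinuation arm, the test is anti-conservative: about 5-6% false NI with 10% missing and a 4 mmHg gap, and about 10-14% with an 8 mmHg gap, against a nominal 2.5%. In the simulation, losing the two highest-mPAP stoppers of 37 was enough for 7.8%.

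These sizes rest on assumed gaps and an assumed arm for the losses. Random loss leaves the error at 2.5%, and selective loss in the continuation arm works against NI. The text leaves the primary conclusion exposed to this bias; it does not show that the bias will occur.

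**What to change.** Replace the blanket statement against imputation with a required sensitivity analysis of the primary endpoint, in both the per-protocol and the ITT set:

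1. Multiply impute missing week-16 mPAP from the baseline-adjusted ANCOVA. In the per-protocol set, include participants who qualify apart from the missing catheterisation.
2. Add a penalty delta to each imputed value in the group analysed as discontinuation, and none in the continuation group.
3. Step delta from 0 through the 4 mmHg margin to at least 8 mmHg. Stopping at 4 is too short: with 10% missing it moves the estimate by only 0.10 × 4 = 0.4 mmHg, half of the 0.8 mmHg bias in the larger scenario.
4. Report the delta at which the upper 95% limit passes 4 mmHg, and whether NI survives over the range.

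Keep the both-arms week-8 rule as the main safety comparison. Beside it, show a worst-case sensitivity version that counts unknown-reason withdrawals as worsened in the discontinuation arm only.

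The cost is revised wording, one extra mPAP analysis and one extra tabulation, with no added participants or visits. The downside is a possibly less favourable sensitivity result.

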### Sample size calculation

The sample size calculation was performed for the primary endpoint, mPAP at 16 weeks, and for the two secondary endpoints highest in the hierarchy (NT-proBNP and 6MWD). Sample size calculations were performed using the formula: n=f(α,β)×2×σ²/d², where f(α,β) = (Φ⁻¹(α) + Φ⁻¹(β))². For the primary endpoint (mPAP at 16 weeks), assuming a one-sided α of 0.025, power of 90%, SD of 4.9 mmHg and an NI margin of 4 mmHg, 64 participants (32 per group) are required. Allowing for a 10% dropout rate, the target sample size for the primary endpoint is 70 participants.

For NT-proBNP, a NI margin of 30% was chosen, reflecting a clinically meaningful change commonly used in PH and heart failure trials.^20–24^ NT-proBNP values from preliminary data were log-transformed (mean 5.04, SD 1.15), corresponding to a NI margin of 1.51 on the log scale. This yielded a required sample size of 26 participants (13 per group) with 90% power and one-sided α=0.025; accounting for dropout, 29 participants are required. For 6MWD, a NI margin of 15% was used, consistent with widely used definitions of clinical worsening in PAH and CTEPH trials. Using a mean of 467 m and an SD of 95 m of riociguat-treated post-BPA patients derived from a study by Wiedenroth *et al*,^25^ 66 participants (33 per group) are required with 85% power and one-sided α=0.025. After allowing for 10% dropout, 74 participants are required. As the largest sample size was required for 6MWD, the total sample size was set at 74 participants.

NT-proBNP was prioritised in the hierarchical testing strategy because it is an objective biomarker that reflects haemodynamic status. Also, the planned sample size provides greater statistical power for NT-proBNP than for 6MWD.

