### Data management, monitoring and confidentiality

All study data will be collected and managed using CastorEDC, a secure, web-based electronic data capture system compliant with Good Clinical Practice (GCP) and the General Data Protection Regulation. Data will be pseudonymised. Access to the study database will be restricted to authorised study personnel. Data quality is ensured through built-in validation checks, predefined range limits and regular monitoring of entered data. Source data verification will be performed for key study variables. Study data will be stored for a minimum of 15 years in accordance with local regulations.

Monitoring will be conducted by an independent team of monitors. A data safety monitoring board will not be established for this study, as it is not considered a high-risk trial and no formal interim analysis is required. The study may be subject to audit by the sponsor, ethics committees or regulatory authorities to assess compliance with GCP.

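### If patients who restart riociguat are lost from the per-protocol set, the planned switch to 2:1 or 3:1 adds under one point of power; the plan must settle how restarters are handled

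*Protocol article*

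**What the plan says.** The Analysis set section makes per-protocol the primary analysis and treats clinical worsening as a source of loss from it. It reports that "the study is expected to retain approximately 80% power if up to 35% of participants are lost from the intervention group". To guard against too little power, the allocation is reviewed once half of the planned patients are included. If at least 30% (or 40%) of the discontinuation arm have restarted riociguat, "the randomisation ratio will be adaptively adjusted from 1:1 to 2:1 or 3:1, respectively, in favour of the discontinuation group". A separate sentence says: "If ≥50% of participants in the discontinuation group experience clinical worsening, the study will be terminated for safety reasons".

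Earlier in the same section, patients who restart because of clinical worsening are assigned to the continuation arm for the primary analysis. That is reassignment, not loss.

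The Sample size calculation section fixes the total at 74, driven by 6MWD. The Data management section explains the absence of a data safety monitoring board partly by saying that "no formal interim analysis is required".

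**The concern.** With a fixed total, a ratio change cannot add patients; it only moves them from control to discontinuation. If restarters are lost, the discontinuation arm needs some enrichment, but too much starves the control arm. The question is whether 2:1 or 3:1 over the second half of recruitment helps, and by how much.

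If it does not help, the plan has a mid-trial adaptation without its intended benefit, and more patients are randomised to the arm whose restart rate triggered the change. It also makes treatment arm correlate with calendar period. The answer depends on whether restarters are lost or reassigned, and the section says both.

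**Working it through.** **Inputs.** "A one-sided significance level of α=0.025 will be used" (Statistical analysis). For mPAP: "power of 90%, SD of 4.9 mmHg and an NI margin of 4 mmHg" (Sample size calculation). For 6MWD: margin 15% of 467 m = 70.05 m, SD 95 m. Total 74. The formula "n=f(α,β)×2×σ²/d²" has no term for a true difference, so a true difference of 0 is assumed throughout.

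**Reproducing the plan's figures.**
- mPAP: (1.960 + 1.282)² × 2 × 4.9² / 4² = 31.5, rounded up to 32 per group. This matches "64 participants (32 per group) are required".
- 6MWD at 85% power: (1.960 + 1.036)² × 2 × 95² / 70.05² = 33.03; the plan states 33 per group.
- Power with 35% lost: Φ(margin / (SD × √(1/n_D + 1/n_C)) − 1.96). For mPAP with 32 per arm, n_D = 32 × 0.65 = 20.8 and power is 0.826. For 6MWD with 37 per arm, n_D = 24.05 and power is 0.804. Either fits the plan's approximately 80%. The article does not say which endpoint or number it simulated.

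**Final arm sizes.** The first 37 patients are split 1:1 (18.5 each) and the last 37 at the new ratio.
- 1:1 throughout: 37 / 37.
- 2:1: 18.5 + 24.67 = 43.2 discontinuation, 30.8 continuation; overall ratio 1.40.
- 3:1: 18.5 + 27.75 = 46.25 discontinuation, 27.75 continuation; overall ratio 1.67.

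**Why the gain vanishes if restarters are lost.** Power depends on n_D(1−L)·n_C / (n_D(1−L) + n_C), where L is the fraction lost.
- L = 30%: 25.9 × 37 / 62.9 = 15.24 at 1:1; 30.2 × 30.8 / 61.0 = 15.26 after 2:1.
- L = 40%: 22.2 × 37 / 59.2 = 13.875 at 1:1; 27.75 × 27.75 / 55.5 = 13.875 after 3:1.

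The overall ratio that maximises this quantity is 1/√(1−L): 1.20 at 30%, 1.24 at 35% and 1.29 at 40%. The rule's 1.40 and 1.67 overshoot it.

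**Power without → with the switch (all 74 evaluable).**

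| Loss, new ratio | mPAP, restarters lost | mPAP, counted as continuation | 6MWD, restarters lost | 6MWD, counted as continuation |
|---|---|---|---|---|
| 30%, 2:1 | 0.890 → 0.890 | 0.918 → 0.932 | 0.821 → 0.821 | 0.857 → 0.877 |
| 35%, 2:1 | 0.876 → 0.879 | 0.908 → 0.926 | 0.804 → 0.807 | 0.844 → 0.868 |
| 40%, 3:1 | 0.860 → 0.860 | 0.896 → 0.925 | 0.784 → 0.784 | 0.828 → 0.867 |
| 45%, 3:1 | 0.841 → 0.845 | 0.880 → 0.915 | 0.762 → 0.766 | 0.808 → 0.854 |

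Even at 49% loss with restarters lost, the gain stays below one point (mPAP 0.823 → 0.830).

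**Exposure and intention-to-treat power.** Expected restarts are n_D × L: 11.1 → 12.95 at 30%, 12.95 → 15.1 at 35%, 14.8 → 18.5 at 40%, 16.7 → 20.8 at 45%. Intention-to-treat power for mPAP falls from 0.940 to 0.933 (2:1) or 0.925 (3:1).

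**Period imbalance.** After 2:1, the second period holds 24.67/43.17 = 57.1% of the discontinuation arm and 12.33/30.83 = 40.0% of the continuation arm, a gap of 0.171. After 3:1 the shares are 60.0% and 33.3%, a gap of 0.267. Without a period term, each 1 mmHg of residual drift between periods therefore shifts the treatment difference by 0.17 or 0.27 mmHg.

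**The case against.** The strongest reply is that the plan's explicit rule counts restarters with the continuation arm, and losing patients from the intervention group is wording that fits that rule too. On that reading the switch does add power, as the table shows. This stands, so it cannot be said without condition that the ratio change buys nothing. Against it, the paragraph that motivates the switch speaks of loss from the per-protocol analysis itself, and on the reassignment reading unswitched mPAP power is already 0.88 or more up to 45% loss. The benefit there matters more for 6MWD.

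Four stronger readings are tempting, and the documents do not support them.
- *One patient separates 3:1 from termination.* With 18 in the arm at the look, 8 restarts is the only count giving 3:1 and 9 is 50%. Half of 74 is 37, so the arm may equally hold 19, where 8 or 9 gives 3:1. More importantly, the ratio rule counts restarts, while the termination rule counts clinical worsening and names no time point.
- *A 30% trigger contradicts power being adequate up to 35%.* A trigger set below the limit is a reasonable buffer.
- *The look contradicts the Data management section.* The look counts restarts in one arm of an open-label trial and tests no hypothesis. It is also openly pre-specified. A cross-reference is needed, no more.
- *Drift will bias the result.* The documents give no drift. The non-inferiority decision uses a baseline-adjusted difference, which absorbs part of any drift, and a period term may sit in an analysis plan not shown. Only the sensitivity per mmHg can be stated.

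**Conclusion.** The concern holds conditionally. If restarters are lost from the per-protocol set, the switch gains under one point of power for mPAP and 6MWD and nothing at 40% loss with 3:1. It places about 6 or 9 more patients in the discontinuation arm, so it does not do the job the plan gives it. If restarters are counted as continuation patients, it gains 1.4 to 3.5 points (mPAP) or about 2 to 4.6 points (6MWD) at 30–45% loss, with the same extra exposure and the same fall in intention-to-treat power. The Analysis set section supports both readings and must be reconciled before the adaptation can be judged.

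The figures assume a true difference of 0, equal SDs, the same loss rate before and after the look, loss unrelated to mPAP or 6MWD, and all 74 patients otherwise evaluable. With 10% dropout (66.6 evaluable) the levels are lower but the pattern is the same: mPAP power at 40% loss, restarters lost, is 0.822 with or without 3:1.

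**What to change.** 1. State one handling of restarters in the primary analysis, and report the simulated power under it with and without the ratio change, naming the endpoint and the number evaluable.
2. If restarters are dropped, delete the ratio change and keep 1:1 throughout. This is a wording change that costs less than one point of power. Baseline adjustment offers more protection for mPAP. If the residual SD were about 3.8 mmHg (an assumption, borrowed from the SD of change in the Non-inferiority margin section), 33 per arm with 40% lost would give Φ(4 / (3.8 × √(1/19.8 + 1/33)) − 1.96) = 0.96. This does not carry over to 6MWD.
3. If the switch is kept, add enrolment period (before or after the change) as a fixed factor in the primary model, beside the stratification factors already named in the Statistical analysis section. The cost is one degree of freedom.
4. Let the Data management section refer to the half-way look by arm.

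None of this touches the termination rule.
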